### Blinding

Participants will be blinded to the implant design used in their operation. Staff on the ward will also be blinded. The physiotherapists conducting the follow-up visits (at 2–3 months, 1 year, and 2 years, i.e., the outcome assessors) will also be blinded to the allocation. The patients will not receive information on the specific implant design used in their operation until all patients have completed the 2-year follow-up visit.

### Statistical methods

Descriptive statistics, including mean and standard deviation, for continuous variables will be used. Differences between groups in continuous skewed main outcome variables will be analyzed using the Mann-Whitney U-test, and t-test when variables are normally distributed. Results will be presented with 95% confidence intervals. Two-way-tables with the chi-square test will be used for dichotomous variables, and multivariate analysis will be conducted with regression analysis. The α-level will be set at 0.05. SPSS Statistics version 23 (IBM Corp., Armonk, NY) will be used for the analysis.

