### Primary and secondary outcome measures

The primary outcome is the Finnish language version of the OKS (33) measured both preoperatively**,** and postoperatively at 2–3, 12, and 24 months. The OKS is a validated and reliable PROM. The questionnaire comprises 12 items regarding pain and activities of daily living (ADL) specifically related to the knee. Each item is scored on a five-level Likert scale 0 (worst disability) to 4 (no disability). The total score can range from 0 to 48, with 48 being the best possible score. The minimal clinically important difference (MCID) depends on the purpose of the comparison: it has recently been defined as 5 points, when different patient cohorts are compared against each other [18, 30, 33, 34]. Thus, in this study, a > 5-point difference in median OKS at 24 months postoperatively between any of the three cohorts studied (Persona CR, PFC CR, and NexGen CR) will be defined as a clinically significant difference in functional outcome.

The secondary measured outcomes both preoperatively, and after surgery at 2–3, 12, and 24 months are the FJS, the 15D, the UCLA activity score, and the VAS pain scale.

The FJS is an assessment tool designed especially for well-performing patients and describes the patients’ ability to forget the artificial joint in everyday life. The questionnaire comprises 12 items regarding and integrating pain, stiffness, function in ADL, patients’ activity levels, and psychosocial factors. Each item is scored on a five-point Likert response format of 1 (never) and 5 (mostly), and scores are summed and linearly transformed to a 0 to 100 scale. The high scores indicate good outcome, equaling a high degree of forgetting the replaced joint during ADL [17, 22, 35]. The validity and reliability of the FJS has been reported to be good, with a lower ceiling effect than the OKS [36].

The 15D is a generic, comprehensive (15-dimensional) self-administered instrument for measuring health-related quality of life (HRQoL)(19). The questionnaire comprises 15 dimensions with 5 ordinal levels on each dimension. From each dimension, the respondents choose the level that best describes their present health status. A set of population-based preference and utility weighs is used to generate the 15D score on a 0 (being dead) to 1 (full health) scale. Moreover, the 15D scores are generalizable and valid for deriving quality-adjusted life years (QALYs). The generic MCID for the change of 15D scores are ±0.15 [19, 37].

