### Sample size

The power analyses will be calculated using both the OKS (primary outcome) and the FJS (secondary outcome). Of these, the FJS is more sensitive in differentiating patients at the upper end of the outcome scores and requires larger patient groups. With the OKS, the estimated sample size is 48 patients per arm. With the FJS in the range of 60 to 80 and a standard deviation of 25 points, the estimated sample size is 64 patients per arm (delta = 13, sd = 25, alpha = 0.05, power = 0.8). Allowing for a 10% drop-out rate and a 10% addition due to skewness in the variable distribution, the required arm size is 80. Therefore, with three comparison arms, the total number of patients recruited into the study will be 240.

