Strict inclusion criteria are a possible limitation of our study and may result in selection bias, as a good number of patients had to be excluded. Therefore, even random allocation may end up in heterogeneity of intervention arms. However, the inclusion criteria are set to focus on the most common type of patient, i.e., patients with primary uncomplicated osteoarthritis of the knee. The upper age limit was set to 70 years to also obtain outcome data on the more active younger TKR patients, who tend to end up at the upper end of the outcome scores after TKR surgery. In theory, this approach might help us to better differentiate “good” outcome from an “excellent” outcome, especially if such subtle differences are found between the implant designs that would not become evident in the older, less active patient groups. On the other hand, if a novel knee design cannot provide these younger and generally more active patients with an improved functional outcome, it will certainly not do so in other patient groups either.

Introducing a new TKR implant system is a known risk factor for failure in joint replacement [40]. This poses the danger of a type 2 error in hypothesis 1, as the surgeons are more familiar with the conventional implant systems and the outcome of the novel TKR design may be inferior due to surgeon-related factors. To avoid this pitfall, we arranged a formal training of the novel implant system and allowed each of the participating surgeons to perform approximately 10 surgeries with the novel implant before commencing the random allocation.

The longevity of contemporary TKR designs is excellent, but the functional outcome and patient satisfaction levels still leave room for improvement. Functional outcome is, however, the result of complex interplay, where the implant design is only one factor and patient characteristics and the surgeon performing the implantation play major roles as well. The development of TKR implants is a continuous activity, where the manufacturing industry plays a leading role. The evaluation of novel designs must be carried out according to strict scientific methods to be able to differentiate the influence of the three major factors – the implant, the patient, and the surgical performance – from each other. In addition, it is especially important to carry out these evaluative studies in independent centers, and not to be biased by the interests of implant manufacturers.

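### The main OKS comparison is an unadjusted two-sample test chosen by the observed distribution; it leaves the preoperative OKS unused and the effect measure open, at a cost in precision but not in validity

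*Protocol article*

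**What the plan says.** In the protocol article, Primary and secondary outcome measures: "The primary outcome is the Finnish language version of the OKS", measured before surgery and at 2–3, 12 and 24 months. The same section makes the criterion for a clinically significant result a difference of more than 5 points in median OKS at 24 months between any of the three arms.

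Statistical methods gives the rule for the comparison: "Differences between groups in continuous skewed main outcome variables will be analyzed using the Mann-Whitney U-test, and t-test when variables are normally distributed." It names no covariate for these tests, no criterion for calling a variable skewed or normal, and no decision for OKS itself. It adds that "multivariate analysis will be conducted with regression analysis", without saying for which outcome, with which covariates, or whether as primary or secondary analysis. On the significance level it says only "The α-level will be set at 0.05".

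Hypothesis (i) is that the conventional and novel designs give similar OKS results. The Discussion stresses having enough patients to rule out a type 2 error if no difference is found.

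**The concern.** There are two linked weaknesses.

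First, the effect measure depends on the data. The t-test compares means; Mann-Whitney compares rank distributions. Neither directly estimates the difference in medians on which the 5-point criterion is set. The quantity tested could thus change with the shape of the observed scores, and in neither case is it the quantity in the criterion.

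Second, neither test can use the preoperative OKS. Where baseline and 24-month scores are correlated, an adjusted comparison gives a narrower interval from the same patients. The Discussion itself expects that the arms may differ despite random allocation.

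Precision matters more than usual here because the trial expects similar outcomes. A finding of no important difference will be only as convincing as its confidence interval is narrow against 5 points.

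**Working it through.** **Inputs from the article (Sample size).** "With the OKS, the estimated sample size is 48 patients per arm"; the difference, standard deviation and power behind it are not given. The final size is 80 per arm with a 10% drop-out allowance, so 80 × 0.9 = 72 evaluable per arm.

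**Assumptions.** Two-sided alpha of 0.05 (sidedness is not stated), an OKS difference of 5 points, power of 0.80, and a baseline-to-24-month correlation ρ of 0.2, 0.3 or 0.5. The article gives none of these for OKS except the 0.05 level.

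**Step 1: the plan's own OKS figure.** The 48 per arm cannot be checked forwards without its inputs, so it is solved for the standard deviation. From n = 2·SD²·(z₀.₉₇₅ + z₀.₈₀)²/Δ²,

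SD = 5 × √(48/2) / (1.960 + 0.842) = 24.49 / 2.802 ≈ 8.74 points.

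With power 0.90 instead, the implied value would be 7.56.

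**Step 2: precision without adjustment.** The 95% half-width for a difference in means between two arms is 1.96·SD·√(2/n) = 1.96 × 8.74 × √(2/72) ≈ 2.86 points. Power for a 5-point difference is 92.9%.

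**Step 3: precision with adjustment.** Baseline adjustment multiplies the residual variance by 1 − ρ² and the half-width by √(1 − ρ²). The equivalent unadjusted sample is 72/(1 − ρ²).

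| ρ (assumed) | 1 − ρ² | Equivalent n per arm | Half-width, SD 8.74 | Power for 5 points |
|---|---|---|---|---|
| none | 1 | 72 | 2.86 | 92.9% |
| 0.2 | 0.96 | 75 | 2.80 | 93.8% |
| 0.3 | 0.91 | 79 | 2.72 | 94.9% |
| 0.5 | 0.75 | 96 | 2.47 | 97.7% |

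The relative narrowing, 1 − √(1 − ρ²), is 2%, 5% and 13% and does not depend on the standard deviation. With SD 7.56 the half-width starts at 1.96 × 7.56 × √(2/72) = 2.47 and falls to 2.42, 2.35 and 2.14.

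**Step 4: does choosing the test from the data distort type I error?** Simulation under no difference, 72 per arm, 6,000 runs: Shapiro-Wilk in each arm, t-test if neither rejects at 0.05, otherwise Mann-Whitney. This is one possible reading, as the article gives no criterion.

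| Distribution | Type I error | t-test chosen |
|---|---|---|
| Normal | 0.0505 | 89% |
| Mild skew | 0.0520 | 32% |
| Strong skew near the ceiling | 0.0468 | 0% |

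The error rate stays close to 0.05 throughout. Under mild skew, however, about one trial in three would report the t-test and the rest the rank test, so which quantity is tested is a matter of the sample drawn.

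**The case against.** The strongest reply is that the article is a condensed account. It does plan regression, and covariates and model details may stand in an analysis plan that is not shown. That is fair as far as it goes: adjustment is unspecified rather than excluded, and absent model details are not a fault. But the article does more than stay silent. It assigns the comparison of the main outcomes to two unadjusted tests and makes the choice depend on the distribution. A regression with no stated outcome or status does not displace that.

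It can also be said that skewness was foreseen, since the sample size carries 10% for it and the criterion is a median, so Mann-Whitney is the likely choice. That reduces the practical uncertainty. It also means that the test could have been named outright.

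The gain is modest as well. OKS power at 72 per arm is already about 93% under the implied standard deviation, and every half-width above lies well inside 5 points. This stands and limits the weight of the point.

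A reader might go further in four directions that the article does not support:

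- **Bias from not adjusting.** Under randomization the unadjusted comparison is unbiased, and chance imbalance is already reflected in the interval.
- **Bias from a complete-case analysis.** The article does not say how missing 24-month scores will be handled; the 10% is a sample-size allowance.
- **Confounding of implant with surgeon.** The Discussion wants to tell apart "the implant, the patient, and the surgical performance", but as a general aim for evaluating new designs. Random allocation balances surgeons in expectation. Unfamiliarity with the new implant is addressed by formal training and about 10 operations per surgeon before allocation began. Surgeon identity is not listed as a study variable.
- **Error in leaving out the 2–3 and 12-month scores.** The criterion is set at 24 months, so a 24-month test need not use them.

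**Conclusion.** The point holds as one of efficiency and prespecification. The stated main comparison makes the effect measure depend on the observed distribution, does not match the median-based criterion, and leaves a recorded baseline score unused. It is a valid test with essentially the nominal type I error.

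The forgone precision is small at a correlation of 0.2 and more useful at 0.5, where the patients evaluated would do the work of a third more. Its size in points rests on an assumed correlation and on a standard deviation solved back from 48 per arm, and it applies to a difference in means. The interval that would accompany a Mann-Whitney test was not computed. Neither the missing test criterion nor the unused baseline makes the planned result wrong. Correcting both is worthwhile because it costs almost nothing and the similarity hypothesis is judged on interval width.

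**What to change.** Before unblinding, name one primary analysis of 24-month OKS that adjusts for preoperative OKS: for example, ANCOVA with arm and preoperative OKS, giving the arm contrasts with robust or bootstrap 95% confidence intervals to allow for skew. Keep Mann-Whitney as a sensitivity analysis and drop the rule that selects the test from the distribution.

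State the 5-point criterion on the scale of that estimate. Either express it as a mean difference to match ANCOVA, or keep the median and make a baseline-adjusted median difference (quantile regression) the primary estimate. Moving to a mean-based model without this step would only replace one mismatch with another.

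Two additions are optional: surgeon as a further term if surgeon identity is recorded, and a repeated-measures model using the 2–3 and 12-month scores in place of ANCOVA.

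The cost is a few sentences in the analysis plan and modest programming. No new data are needed for OKS. Time schedule gives August 2018 as the end of recruitment, so 24-month follow-up runs to at least August 2020, and the change could still be recorded before unblinding when the article appeared in October 2019.

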### Study material

All the information and gathered material will be stored in a study registry at Coxa Hospital for Joint Replacement. The registry will be protected with passwords that will only be given to the authors and the secretary of the study group. All study data will be deleted 15 years after the end of the study, as required by Finnish law.

### Time schedule

Recruitment for the study began in September 2015 and was completed in August 2018. The results of the study will be analyzed after 2-year follow-up, and the final report will be published by the end of 2021.

## Discussion

This paper presents a prospective, randomized controlled trial comparing a novel TKR implant design with conventional TKR designs in terms of functional outcome and cost-effectiveness. It describes details of patient randomization, PROMs, follow-up, aftercare and methods of analysis of the material, and publication plan. The strengths of our study include its pragmatic nature and validated outcome measures, with an emphasis on PROMS. We included several aspects of outcome to capture the whole picture of patient satisfaction and to obtain data on the economic aspect for cost/benefit analyses.

The adequate number of patients is a very critical question. According to power analysis, our study design allows us to have sufficient numbers of patients to confirm or reject the research hypotheses on primary outcome measures. This is especially important if the results turn out to show no differences between the study arms – to avoid speculation on the possibility of a type 2 error. The economical aspect is also important as the novel designs are substantially more expensive, and therefore the benefits of the additional costs are of great interest to all health care providers.

Maintaining blinding of study arms is challenging in all studies that assess the outcomes of surgical procedures. Successful blinding of the patients is critical because PROMS are the key outcome tools. We discussed the nature and importance of blinding with the patients before they consented to participate in the study. The follow-up visits are being carried out by physiotherapists who are dedicated to research projects, and their perfect blinding is also challenging and depends largely on their commitment to the study philosophy.

Strict inclusion criteria are a possible limitation of our study and may result in selection bias, as a good number of patients had to be excluded. Therefore, even random allocation may end up in heterogeneity of intervention arms. However, the inclusion criteria are set to focus on the most common type of patient, i.e., patients with primary uncomplicated osteoarthritis of the knee. The upper age limit was set to 70 years to also obtain outcome data on the more active younger TKR patients, who tend to end up at the upper end of the outcome scores after TKR surgery. In theory, this approach might help us to better differentiate “good” outcome from an “excellent” outcome, especially if such subtle differences are found between the implant designs that would not become evident in the older, less active patient groups. On the other hand, if a novel knee design cannot provide these younger and generally more active patients with an improved functional outcome, it will certainly not do so in other patient groups either.

Introducing a new TKR implant system is a known risk factor for failure in joint replacement [40]. This poses the danger of a type 2 error in hypothesis 1, as the surgeons are more familiar with the conventional implant systems and the outcome of the novel TKR design may be inferior due to surgeon-related factors. To avoid this pitfall, we arranged a formal training of the novel implant system and allowed each of the participating surgeons to perform approximately 10 surgeries with the novel implant before commencing the random allocation.

The longevity of contemporary TKR designs is excellent, but the functional outcome and patient satisfaction levels still leave room for improvement. Functional outcome is, however, the result of complex interplay, where the implant design is only one factor and patient characteristics and the surgeon performing the implantation play major roles as well. The development of TKR implants is a continuous activity, where the manufacturing industry plays a leading role. The evaluation of novel designs must be carried out according to strict scientific methods to be able to differentiate the influence of the three major factors – the implant, the patient, and the surgical performance – from each other. In addition, it is especially important to carry out these evaluative studies in independent centers, and not to be biased by the interests of implant manufacturers.

## Data Availability

The datasets used and/or analyzed during the current study will be available from the corresponding author on reasonable request once the study has been completed.

## Abbreviations

ADL: Activities of daily living
CR: Cruciate retaining
FJS: Forgotten joint score
HRQoL: Health-related quality of life
MCID: Minimal clinically important difference
NICE: National Institute of Healthcare and Clinical Excellence
OA: Osteoarthritis
OKS: Oxford Knee Score
PROM: Patient-reported outcome measure
PS: Posterior stabilized
QALYs: Quality-adjusted life years
SPIRIT: Standard Protocol Items: Recommendation for Interventional Trials
TKA: Total knee arthroplasty
TKR: Total knee replacement
UCLA: University of California Los Angeles
VAS: Visual-Analogue-Scale
